### Secondary outcomes

In order to assess the commitment of the *social network,* The Parenting Support Questionnaire (PSQ) [25] will be used to assess perceived support of the social network. Additionally, social support concerning well-being and housing will be assessed with the Interpersonal support evaluation questionnaire - short (ISEL) [26]. Additionally, the changes in social support will also be addressed with the Succint questionnaire [8].

The *perceived control* will be assessed with an interview concerning perceived control by the researcher. Parent, EK-coordinator, Family manager and a member of the network will be interviewed. Additionally, Perceived control will be assessed with the Succint [8]. Finally, empowerment of the parents will be assessed with the Family Empowerment Scale (FES) [27].

The *quality of family functioning* will be assessed with the Parenting Stress Index Short form [28]. This instrument assesses parental stress in child rearing situations. Additionally, family functioning in terms of problem definition and reason to search help is registered with the FG-checklist, an instrument standard used in the FG working procedure. Additionally, the Family Assessment Device (FAD) [29], consisting of 12 items, will be used to assess quality of family functioning. Moreover, file analysis will be used to identify family functioning issues.

Finally, Basic Needs Satisfaction in General Scale (BNSG-S) will be used to assess ’satisfaction of basic psychological needs’ [30]. This questionnaire consists of three subscales: autonomy, competence and social connectedness. This instrument is translated to Dutch [31] and validated for a mentally delayed population. Additionally, the Satisfaction with Life scale [32], consisting of 5 items, is used to assess general well-being of parents.

Finally, the use of professional care will be retrieved from files at each of the 5 assessment points. Trained coders will code the use of professional care.

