Research that did include a (not in all respects equivalent) comparison group [9], found that families that had participated in a FG-c reported less concerns about safety and well-being of the children and that social support from the network had increased. However, the changes in the Family Group-conferencing group were not larger than in the control group, and several methodological flaws of the study (e.g., short follow-up time, non-equivalence of the experimental and control group, high drop-out rates, lack of statistical power, and inadequate statistical analyses) did impose significant limitations on the causal inferences that could be drawn.

Notably, studies examining FG-cs show inconsistent results. Some researchers found positive effects of FG-c’s on short-term but no long-term effectiveness [10]. Where Burford et al. (2013) reported positive results of FG-c, Lorentzen (2009) and Sundell et al. (2004) did not find evidence for the effectiveness of FG-c’s [11-13]. Berzin et al. (2008) reported negative outcomes: families who had participated in FG-c had adverse outcomes for safety and stability of out of home placements and frequently refused necessary youth care [14]. A recent systematic review including only controlled studies, of which only six were available, showed that FG-c’s lead to an increase in child abuse, more and longer out of home placements and ultimately to an increase in use of professional care [15].

To conclude, although much research has been done to investigate FG-cs, there is still insufficient evidence for its effectiveness, in particular because of the use of weak study designs [16]. Research with a robust design does not confirm the positive findings reported in the uncontrolled studies [15]. Worldwide, only six studies including a control group have been conducted. It is therefore crucial to conduct a study that allows for conclusions on causality about the effects of FG-c’s.

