## Methods and design

The study aims to answer two main questions. The first question is whether Family Group conferences in youth care are effective as a decision making model in terms of increased child safety, involvement of the social network, perceived control over problems and a reduction in use of professional care. In order to determine the effectiveness of FG-cs, a RCT will be carried out including 300 families referred to Youth Care Agency Amsterdam (YCAA). Moreover, costs associated with FG-c will be identified in order to determine the cost-effectiveness of FG-cs.

The second research question concerns the moderators of the effectiveness of FG-c. Both participant and program characteristics will be examined as potential moderators. Program characteristics to be examined are program integrity and characteristics of FG coordinators and family managers (responsible for supporting the implementation of the FG plans developed by the broader social network of the family). It is crucial to examine program integrity (i.e., the extent to which different phases of a FG-c have been conducted according to the protocol). Without having established program integrity, there is the risk of concluding that FG-cs are not effective, whereas in fact the FG-c has not been fully implemented. Furthermore, it is possible that a successful FG-c has taken place, but the plan developed in the FG-c has never been carried out. It is therefore important to determine whether all stages of the FG-c have been implemented as planned.

Additionally, it is important to examine family characteristics as potential moderators of the effectiveness of FG-c. It is plausible that FG-cs are not equally effective for every participating family. For example, families with a small social network, or with limited possibilities to attend a conference or with other particular characteristics that hamper the organization or carrying out of a FG-c or the FG plans are less likely to attend a FG-c. Identifying those families who are less likely to fulfill an FG-c may result in savings.

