### Design

A randomized Controlled trial will be conducted to examine whether FG-cs are effective in changing: (1) child’s safety (i.e., decrease in (risk for) abuse/neglect; less supervision orders or shorter supervision order; less or shorter out of home placement); (2) the involvement of the broader social network; (3) perceived control over the problems in the families, empowerment of parents; improvement of family functioning; (4) less use of professional care. A second aim is to study whether the effectiveness of FG-c is influenced by characteristics of the implementation of the methodology, characteristics of the family managers (such as education, or attitude towards FG-c), or by family characteristics (such as size of the social network, ethnicity or family type: single/married).

Using computerized randomization two comparable groups will be formed. Until the inclusion of 300 families is completed (presumably within 6 months), every family starting care at Youth Care Agency Amsterdam (YCAA) will be randomly allocated to care with or without a Family Group conference. Because allocation to care with a FG-c will not always result in an actual Family Group conference and/or an approved Family Group plan, 200 families will be assigned to care with FG-c and 100 families to care without FG-c. Five multi-informant/source (parent, family manager; FG-coordinator; member of the family’s social network; child (if > 8 years of age), and file analysis) assessments will be carried out in both groups. Pre-tests will take place before FG-cs starts. Subsequently, in both groups post-tests will be carried out 1, 3, 6 and 12 months after the FG-c has taken place (see also Figure 1 for the flow chart).

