### Control condition

In the control condition, the family will receive the usual care. This means that the family manager is the one who designs and organizes the care plan instead of the family. YCAA works according to Generic Family oriented method since 2011: child protection, juvenile probation and youth are no longer distinguished. Employees (former youth probation workers, youth care workers and child protection workers) have been retrained as family managers (FM), who are able to provide the needed care to a family (or by referring to other professional services). As in the experimental condition, in the control condition, family managers will also work with a care plan. The difference between the FG-c and the control condition lies in the manner in which the plan is established: In the control condition, this is done by the family manager, along with parents/family, they discuss problems in the family and formulate goals, strict agreements are made on what professional help will be started. Within the FG-c, the plan is made by the family and social network. In a Family Group plan, they explain how they see the solution to their problems and what steps they will undertake to solve the problems, including starting professional care. In the intervention and control conditions, the role of the family manager is actually the same: a family manager works in both conditions with the care plan that has been developed, however, the levels of control differ: in the FG-c condition, control over the plan is with the family, in the TAU condition, control is with the family manager.

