### Instruments

An overview of the concepts, instruments and sources of information is presented in Table 1. At the 5 assessment points, the family manager, a member of the network, parent, the family group coordinator and the child (if older than 8 years) will be asked to answer questions, either online, or by telephone. The families and child will receive assistance when filling out the questionnaires.

**Table 1 T1:** Concepts, instruments and informants at the different assessment points

	**Domain/concept**	**Instrument**	**Test**					**Source**					
			**T1**	**T2**	**T3**	**T4**	**T5**	**FM**	**MN**	**P**	**FGC**	**R**	**C**
Primary outcome													
	Safety	LIRIK	x		x	x	x	x	x				
		Safety line	x	x	x	x	x	x					
		CAPI	x		x		x	x	x	x			
		Succint		x		x	x	x	x	x			
Secondary outcomes													
	Commitment	PSQ	x	x	x	x	x	x		x			
		ISEL	x	x^1^	x^1^	x	x	x					
		Succint	x	x^1^	x^1^	x	x	x		x			
	Control/empowerment	Interview	x	x	x	x	x	x	x	x			
		Succint	x	x	x	x	x	x					
		FES	x	x^1^	x^1^	x	x	x					
	Family functioning	PSI	x^1^	x^1^	x^1^	x^1^	x^1^		x				
		Succint	x	x	x	x	x	x					
		FES	x	x^1^	x^1^	x	x	x					
	Family functioning	PSI	x^1^	x^1^	x^1^	x^1^	x^1^			x			
	Professional care	File research	x	x	x	x	x					x	
Cost- effectiveness	Costs	Cost questionnaire	x			x	x			x			
Moderators													
Characteristics implementation FG-c and family manager	Number of families	Registration form	x	x	x	x	x					x	
	Role FM	Registration form		x	x	x	x	x	x	x	x	x	
	Chacareristics FM	Registration form	x									x	
	Time to FG-c	File analysis	x	x								x	
	Number members network at FG-c	Registration form		x							x	x	
	Phases FG-c/plan carried out as intended	Registration form	x	x	x	x		x			x	x	
Characteristics families	Demograpgics	File research/questionnaire	x	x	x	x	x	x		x		x	
	Risk factors	Risk factors List	x					x		x		x	
	Problems child	BPC (if child > 8)	x			x	x						x

*Note*: T1 = pretest (questionnaire); T2 = post-test after 1 month (interview by telephone); T3 = post-test after 3 months (interview by telephone); T4 = post-test after 6 months (questionnaire); T5 = follow-up assessment after 12 months (questionnaire); FM = Family Manager; MN = member network; P = Parent; FG-c = Family Group-conference; FGC = Family Group Coordinator; R = researcher; C = Child; ^1^ = selection of the original instrument.

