### Cost-effectiveness

In addition to the primary and secondary outcomes, the costs of family group conferencing will be assessed with an adapted version of the questionnaire for Costs associated with Psychiatric Illness, developed by the Trimbos Institute (TiC-P) [33]. Items concerning social care and youth were added, as Jansen et al. (2013) did [34]. Both direct costs, those costs associated with the intervention (staff costs, overhead, contacts with others, travel costs) and direct cost associated with the youth care utilization (as indicated by parents) as well as indirect costs in terms of productivity loss will be assessed.

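### Professional care use is read from files only and less use is scored as benefit: file completeness may differ by arm, and refused necessary care would count as improvement

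*Protocol article*

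**What the plan says.** The Secondary outcomes section states that "the use of professional care will be retrieved from files at each of the 5 assessment points" and adds "Trained coders will code the use of professional care". Table 1 (Instruments) agrees. The only instrument listed for professional care is "File research", at T1 to T5, with a single source mark that appears to fall in the researcher column.

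The favourable direction is also fixed. Methods and design names "a reduction in use of professional care" among the terms in which FG-c is to be judged effective. Design lists "4) less use of professional care" as one of four targets, and Background names the same aim. None of these places qualifies it.

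Three other statements bear on the point:

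- **Control condition:** the Family Group plan sets out "what steps they will undertake to solve the problems, including starting professional care". The Conditions section makes the network responsible for carrying out that plan; in usual care the family manager has that responsibility.
- **Background:** adverse results of an earlier study are described, among them that FG-c families "frequently refused necessary youth care".
- **Cost-effectiveness:** the adapted TiC-P covers "direct cost associated with the youth care utilization (as indicated by parents". Table 1 schedules this cost questionnaire at T1, T4 and T5, with the parent as source.

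**The concern.** Care use is one of four named effectiveness targets. A file count is a fair comparison only if files record care equally well in both arms. Here the intervention changes who decides on and organises care, which could change what reaches the file. Randomisation and intention-to-treat analysis would not remove such a difference, because it arises after allocation and through the treatment itself.

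The second problem is one of meaning. A lower count can reflect care that is no longer needed, care replaced by the network, or needed care that was refused. The first two are what FG-c aims for. The third is a harm that the article itself reports. At stake is whether a lower count in the FG-c arm can be presented as a success.

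**Working it through.** The article gives no mean, standard deviation, recording rate or expected difference for care use, so there is no figure to reproduce. The sample-size statement (300 families, *d* = .35) does not enter this point.

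**1. When file-only measurement would distort the comparison.** Let *U*F and *U*C be true mean use in the FG-c and control arms, and *c*F and *c*C the fractions that files record. Then

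observed ratio = (*U*F / *U*C) × (*c*F / *c*C).

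The distortion is the factor *c*F / *c*C. If the fractions are equal it is 1 and the ratio is undistorted, however incomplete the files are. If *c*F is smaller, equal true use appears as a reduction under FG-c.

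**2. What the article says about the two fractions.**

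- *Control:* the family manager draws up the care plan with the family, firm agreements are made on which professional help will start, and the manager is responsible for implementation. The person who arranges care also works with the plan.
- *FG-c:* the family and network make the plan, which may include starting professional care. The network is responsible for carrying it out. The family manager approves its safety and monitors it in contact with the responsible network member.

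So the manager follows the plan in both arms, but in the FG-c arm learns of care that someone else arranged, partly through a third person. That makes *c*F < *c*C plausible without establishing it.

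**3. Dilution.** The Design section expects that allocation to FG-c will not always lead to a conference or an approved plan. Let a share *p* of the FG-c arm have a plan, with recorded fraction *c*plan. Assume that the other families are recorded as in control. Then

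*c*F / *c*C = 1 − *p* × (1 − *c*plan / *c*C).

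For *p* below 1, any distortion at arm level is smaller than among families with a plan. The article gives none of *p*, *c*plan or *c*C, so no size can be stated.

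**4. The scoring direction.** Take three FG-c families with the same low file count: one no longer needs care, one has it replaced by the network, and one refused care it needed. All three contribute equally to a lower mean. Under the stated objective all three move the result towards effectiveness. The Statistical analyses section describes a separate ANCOVA for each outcome, which does not distinguish them. This step needs no assumption about file completeness.

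**5. What is already collected.** Files cover T1 to T5. Parent-reported care covers T1, T4 and T5 but is assigned to the cost analysis. A cross-check is therefore possible at three of the five assessments without a new instrument.

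**The case against.** A reader might infer that files do miss care arranged by FG-c families and that the outcome is therefore biased towards FG-c. The documents do not support that. The FG-c plan is the only treatment plan. Any professional care in it is known to the family manager, who must approve its safety and then monitors it, and the Control condition section describes the manager's role as the same in both arms. Only care outside the plan, or care whose start is not reported back, could be lost, and control families can also arrange care outside their plan. The text says only files. The Moderators section mentions the YCAA file when discussing demographics, so agency files are the natural reading but not a stated one. All of this stands and limits the first half of the point to a risk. What remains is that the FG-c manager did not arrange the care and depends partly on the network for information. The Moderators section also accepts that the agency file can lack demographic information and fills those gaps by questionnaire.

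A reader might also infer that the trial would declare FG-c successful because families refused care, or that its conclusion on savings rests on incomplete files. Neither follows. No rule declares effectiveness on this outcome alone. Child safety is primary and, as the Design section defines it, includes abuse risk, supervision orders and out-of-home placement, where harm from refused care should show. The cost analysis draws on parent-reported use.

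Finally, coding details may sit in a fuller document. That is accepted. The point concerns the source and the favourable direction, which the article does fix.

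**Conclusion.** The point holds in two parts of unequal strength. Scoring any reduction as effectiveness, when the article itself cites refusal of necessary care as an adverse result, is a weakness on the face of the text. File completeness that differs by arm is a plausible risk, resting on the inference that care organised by the network reaches the file less reliably than care organised by the family manager. Its size cannot be derived from the documents, and it is nil if recording is equal in both arms. The outcome is secondary and child safety is measured alongside it, so the trial's main conclusion is not at risk. What is affected is how far a lower care count may be claimed as a benefit. The change is worth making because the checking data are already planned.

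**What to change.** 1. Keep file coding as the main source at all five assessments.
2. Pre-specify an arm comparison at T1, T4 and T5 based on the parent-reported care items of the adapted TiC-P, alone and combined with the files. Report agreement between the two sources separately by arm; a difference in agreement between arms would be a warning that recording differs.
3. Where files record care that was indicated but refused or not started, have the coders code it as a separate category.
4. State that lower care use will be interpreted as a benefit only alongside the child-safety results of the same comparison, and will otherwise be reported as *less care received*.

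The cost is one extra coding category, one additional analysis and a sentence on interpretation, with no new data source. The limits should be stated: parent report covers three of five time points, carries recall error and comes from parents who know their arm. It can therefore check the file result but not replace it. The refusal category can only be as complete as the files, so it will not capture every refusal.

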### Cost-effectiveness

In addition to the primary and secondary outcomes, the costs of family group conferencing will be assessed with an adapted version of the questionnaire for Costs associated with Psychiatric Illness, developed by the Trimbos Institute (TiC-P) [33]. Items concerning social care and youth were added, as Jansen et al. (2013) did [34]. Both direct costs, those costs associated with the intervention (staff costs, overhead, contacts with others, travel costs) and direct cost associated with the youth care utilization (as indicated by parents) as well as indirect costs in terms of productivity loss will be assessed.

### Moderators

*Characteristics of the Family Group-conferences (FG-c)*, such as number of families per FG-coordinator, location, time to start of FG-c, number of members of the network present at the FG-c, will be registered on the registration form developed for this specific study.

Additionally, specific characteristics of the Family Group-conference, related to the *implementation of the FG-c*, will be registered on this form too, such as whether the separate phases of the FG-c have been followed as intended, duration of these phases, and whether the plan is carried out as intended and who was responsible for the carrying out of the plan, and whether this person took the assigned role.

Moreover, the *role of the family manager* in the carrying out of the FG-c will be monitored with the registration form: did the family manager bring the FG-c up within the intended period of time (2-6 weeks after start)? Was the family manager supportive of FG-c (and why (not))? Did the Family manager leave control with the family (and why (not))?

*Characteristics of the families* that may affect the effectiveness will be assessed. Demographics will be coded from the file research and information that is not present in the YCAA file will be asked with a questionnaire. Risk factors will be assessed with a risk list that consists of a combination of the Washington Prescreen Risk Assessment instrument [35], for the penal law cases and the Delta risk list specifically developed for civil law cases.

*Problems of the child* will be assessed with the Brief Problem Checklist [36], to be filled out by the parents (if the child is younger than 8 years of age) or the child (if the child is older than 8). This is a validated short questionnaire that assesses problems of the child.

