### Study sample

We aim to include *N* = 300 families, who will be randomized in a 2 (FG-c): 1 (control group) ratio to ensure that there is enough power to also conduct the planned moderator analyses. These groups are large enough to detect effects of FG-c’s.

Given the goal of YCAA to carry out 800 FG-c’s each year, the inclusion of 300 families will be completed within six months. This sample size is sufficient to test the hypotheses with an alpha of .05 and a small to medium effect (*d* = .35). FG-c can be used for all families, so there are no exclusion criteria in this study.

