### Conditions

#### ***Family group- conference [in Dutch: Eigen Kracht-conferentie]***

A Family Group - conference (FG-c) is defined as an approach to care that allows citizens to keep responsibility over decisions on issues within the family, neighborhood, or group of people in which they operate (Oosterkamp Szwaycer et al., 2012). FG-c provides citizens the opportunity to make a plan, using their own capabilities and by using support from outside. This research will focus on FG-cs that are used in youth care as a decision-making model in which families together with others in their social network, such as extended family, neighbors, friends and others, make a plan to solve their problems. The responsibility for making the plan lies within the (extended) family and the social network. Professionals are involved only in order to determine whether the plans developed by the family group are sufficiently safe for the children and to provide information about professional help options.

The Program Bureau responsible for FG-cs (in Dutch: Eigen Kracht Centrale), a national organization that supports and performs FG-c’s, organizes the family group conferences. The FG-c Program Bureau organizes the recruitment and training of the FG coordinators and contracts FG coordinators for the duration of a conference. Family managers thus request a FG-c at the FG-c Program Bureau. The FG coordinator organizes the FG-c in close cooperation with the family and family manager. The FG coordinator is independently associated with the FG-c Program Bureau and is thus not employed by a professional youth care facility.

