### Statistical analyses

Missing data will be imputed so that all participants will be included in the analyses, and using LISREL 8.8, the multiple imputation will be carried out by the expectation maximization algorithm [37]. Both an intention to treat as well as a completer analysis will be performed.

In order to examine the effectiveness of FG-c overall effectiveness will be examined for all outcome measures by conducting an ANCOVA, with the outcome measures at post-test as dependent variables, treatment condition as factor and pre-intervention scores of the outcome variables as co-variates, as is recommended for RCTs using pre- and post-tests [38]. Effect sizes will be computed as Cohen’s d, based on adjusted means and standard errors.

For categorical moderator analyses, the same ANCOVA’s will be conducted, with the moderators as factor. Post-hoc analyses for moderator effects will be conducted by splitting the file according to the moderator and again conducting an ANCOVA and calculating effect sizes separately for each group. Regression analyses will be conducted for the continuous moderators.

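### The planned ANCOVA treats families as independent, although FG coordinators work only in the FG-c arm and may serve several families; if they do, the standard error is probably understated

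*Protocol article*

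**What the plan says.** All references are to the protocol article.

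- **Conditions, Family group-conference:** "The FG coordinator organizes the FG-c in close cooperation with the family and family manager". The Program Bureau recruits and trains coordinators and contracts them conference by conference. How often one coordinator is used again is not stated.
- **Control condition:** the family manager draws up the care plan with the family. No coordinator has a care role there.
- **Moderators:** the registration form is to record "number of families per FG-coordinator".
- **Methods and design:** the program characteristics to be examined as moderators include "characteristics of FG coordinators and family managers".
- **Statistical analyses:** the model for every outcome is an ANCOVA with "treatment condition as factor and pre-intervention scores of the outcome variables as co-variates". Moderators are handled by the same ANCOVA or by regression. No coordinator term, robust standard error or arm-specific variance is named.
- **Study sample and Design:** "We aim to include *N* = 300 families", of whom "200 families will be assigned to care with FG-c and 100 families to care without FG-c". The size is called sufficient "with an alpha of .05 and a small to medium effect" of d = .35. No design effect is mentioned.

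**The concern.** Families served by the same coordinator may resemble one another in outcome. Any such clustering sits in the FG-c arm alone, because control families have no coordinator (a partially nested design). Coordinator variance therefore does not cancel when the arms are compared. An ordinary ANCOVA assumes independent families and one residual variance. With shared coordinators and a positive ICC it tends to give a standard error that is too small, an interval that is too narrow and a type I error above .05.

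The problem is sharper for coordinator characteristics. Such a characteristic takes one value per coordinator, so the information comes from the number of coordinators, yet the planned tests would count families. Moderators are one of the study's two main questions.

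The article itself makes the issue live. Families per coordinator can moderate an effect only if it varies, so the authors expect some sharing. Studying coordinator characteristics as moderators presumes that outcomes may differ by coordinator.

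**Working it through.** **1. The plan's own sample size.** Inputs from the article: 200:100 families, d = .35, alpha .05. Assumed, because not stated: two-sided test, 80% power. For independent families the requirement is 97 control + 194 FG-c = 291, and 200:100 gives 81.5% power. The stated 300 is thus reproduced by a calculation without any clustering allowance.

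**2. Inputs that the article does not give.** m = trial families per coordinator, and ICC. Assumed ranges: m = 1 to 10, ICC = .02 to .10.

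**3. Main contrast.** Set the residual variance to 1 in both arms and add a coordinator variance t = ICC/(1 − ICC) in the FG-c arm.

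- True variance = (1 + t)(1 + (m − 1)ICC)/200 + 1/100
- ANCOVA variance ≈ [(200(1 + t) + 100)/300] × (1/200 + 1/100)
- Ratio R = √(true/ANCOVA); type I error = 2(1 − Φ(1.96/R))

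Example, m = 5, ICC = .05: t = .0526. True = 1.0526 × 1.20/200 + .01 = .01632. ANCOVA = 1.0351 × .015 = .01553. R = 1.025, type I error 5.6%.

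| m | ICC .02 | ICC .05 | ICC .10 |
|---|---|---|---|
| 1 | 0.997 (4.9%) | 0.991 (4.8%) | 0.983 (4.6%) |
| 2 | 1.000 (5.0%) | 1.000 (5.0%) | 1.000 (5.0%) |
| 3 | 1.003 (5.1%) | 1.008 (5.2%) | 1.017 (5.4%) |
| 5 | 1.010 (5.2%) | 1.025 (5.6%) | 1.050 (6.2%) |
| 10 | 1.026 (5.6%) | 1.066 (6.6%) | 1.130 (8.3%) |

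If total variance is instead equal in both arms, the ratios are slightly higher: at ICC .10, 1.017 for m = 2 and 1.142 for m = 10.

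**4. Simulation of the planned ANCOVA** (pre-post correlation .5, no treatment effect, all 200 FG-c families clustered). Type I error over separate runs:

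- m = 5, ICC .05: 5.5% to 5.8%
- m = 5, ICC .10: 6.5% to 6.6%
- m = 10, ICC .05: 6.9% to 7.4%
- m = 10, ICC .10: 9.0% to 10.0%

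The last lies above the formula's 8.3% because baseline adjustment removes residual variance (1 falls to 1 − .5² = .75) but not coordinator variance. With .75 and t = .111, true = (.75 + 10 × .111)/200 + .75/100 = .01681. ANCOVA = [(200 × .861 + 100 × .75)/300] × .015 = .01236. R = 1.166, type I error 9.3%.

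**5. Only half the FG-c arm has a conference.** The formula of step 3, with clustering in 100 of the 200 families, gives:

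- m = 5, ICC .05: R = 1.013, type I error 5.3%
- m = 10, ICC .05: R = 1.034, 5.8%
- m = 10, ICC .10: R = 1.07, 6.7% (about 7% by simulation)

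**6. Coordinator-level predictor.** R = √(1 + (m − 1)ICC). At m = 3, ICC .02: √1.04 = 1.02, type I error 5.5%. At m = 10, ICC .10: √1.90 = 1.38, type I error 15.5%.

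**7. Power.** With equal total variance and no gain from the baseline covariate, variance = (1 + (m − 1)ICC)/200 + 1/100. For 80% power at d = .35 it must not exceed (.35/2.80)² ≈ .0156, so power drops below 80% once (m − 1)ICC exceeds about .12.

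**The case against.** **Sharing is not documented as fact.** A reader might infer that every coordinator serves several trial families. The article only names a variable to be registered. Contracting by conference is compatible with m near 1, and a coordinator's caseload may include families outside the trial, since the agency aims at 800 conferences a year. This stands: the point must be conditional. It does not remove the point, because the article plainly foresees some sharing.

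**Small clusters do no harm.** At m = 1 the ANCOVA standard error is slightly too large, and at m = 2 the understatement is nil or negligible. This stands. The upper figures need m = 10 with ICC .10, and neither is documented.

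**Not all FG-c families have a coordinator.** The Design section says that allocation to FG-c will not always lead to a conference, and an intention-to-treat analysis is planned. Step 5 shows the dilution. It should be smaller in the planned completer analysis.

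**The coordinator's influence is limited.** The plan is made in a private part without the coordinator, and the family manager judges its safety. This argues against assuming a large ICC, not for assuming zero.

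**Family managers.** A reader might also infer that intervals on every outcome are certainly too narrow. Managers work in both conditions and rate much of the primary outcome. If managers hold families in both arms, their shared effect largely cancels from the contrast but stays in the residual, so ignoring it tends to make the standard error too large. The net direction is therefore not established.

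**A condensed article.** Random effects and degrees of freedom are often left to a full analysis plan, which is not shown and may add a coordinator term. But the article does state a model, and that model does not fit the structure it describes. It is also true that coordinator characteristics appear as moderators in the opening of Methods and design, whereas the Design section's own list names only family managers.

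**Conclusion.** The point holds in conditional form. The stated ANCOVA and sample size make no allowance for coordinator clustering in the FG-c arm. If coordinators are shared by about three or more trial families and outcomes differ between coordinators, the standard error of the treatment contrast is understated, leaving family-manager effects aside.

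- **Main contrast:** under the assumed m of 3 to 10 and ICC of .02 to .10, the true standard error is about 0.3% to 13% larger. Type I error is 5.1% to 8.3% by formula and up to about 10% by simulation in the worst case.
- **Coordinator characteristics:** the true standard error is 2% to 38% larger and type I error 5.5% to 15.5%. This is the clearest consequence.

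These figures are a range over assumptions, not an estimate for this trial. For the main contrast the defect is moderate at most and may be negligible. It still merits correction, because without the coordinator's identity the clustering cannot be examined afterwards.

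**What to change.** - Record a coordinator ID on the registration form that already collects coordinator data.
- Replace the plain ANCOVA with a partially nested mixed model: the same fixed effects, a coordinator random effect in the FG-c arm only, control families and FG-c families without a coordinator as single units, and a separate residual variance for each arm. Use Satterthwaite or Kenward-Roger degrees of freedom.
- Test coordinator characteristics against the variance between coordinators, not between families.
- State the m and ICC assumed when calling the sample size sufficient.

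The cost is one data field and a few sentences of analysis text. If clustering is present, intervals widen, by about 0% to 13% for the main contrast under the assumptions above. If coordinators prove not to be shared, or their variance is near zero, the result should be close to that of the ANCOVA.
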